## Background

In the UK, Type 2 diabetes is an increasingly prevalent chronic illness (prevalence now over 3% [1], equating to approximately 50 patients per full time general practitioner). It is an important cause of avoidable mortality. Patients are managed by the integrated activities of clinical and non-clinical members of the primary care team. There are National Institute for Health and Clinical Effectiveness (NICE) guidelines defining standards of care, but studies of the quality of care for patients with diabetes suggest less than optimum care in a number of areas [2]. Quality and outcomes framework (QOF) data for 2004 and 2005 suggest high rates of measurement of clinical and biochemical parameters but lower rates of acting on the results. Only 67% of practices achieved the target of 50% of patients having their hemoglobin A1c (HbA1c) within the target range; the similar figure for blood pressure (BP) (target of 55%) was 70%. Some of this variability will reflect patient physiology/behaviour, but it will also reflect variable clinical management behaviours. General practices, although relatively small organisations, have become more complex in terms of their structures and functions. Few studies have examined factors underlying the organisation and delivery of care in general practice, and only one UK study related them to clinical data [3] demonstrating that team climate, booking interval, and practice size together explained 31% of the variance in diabetes management. These authors, along with others [4,5], identified the need for a better understanding of the relationship between the quality of patient care and individual and organisational factors.

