### Predictor variables

#### Data relating to practice organisational structure

We will collect details of practice structures and function informed by previous studies [3,5]: practice demographics (including practice list size; training status of the practice, and postcodes covered); routine booking intervals for patient consultations; staffing levels of practice staff (numbers of, and number of sessions worked by, doctors, practice employed nurses, and administrative staff); skill mix (ratio of doctors to non-medical clinical staff, and of clinical to administrative staff); organisation of care for the clinical conditions (including specialisation within the clinicians).

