#### Data held within practice computers on the performance of clinical behaviours and measures of physiology

These data will be collected in two ways. First, for all registered patients with diabetes we will collect data on the total number of patients with diabetes in the practice and the number who have had: a foot check; BP, HbA1c, cholesterol, and weight measured; level of systolic and diastolic BP, level of HbA1c, level of cholesterol, and body mass index; diabetes-related medication (hypoglycaemic drugs, lipid-lowering drugs, weight-reducing drugs); advice about self-monitoring and education.

Second, we will collect QOF scores for diabetes and for additional items that reflect aspects of good organisation and that, on the basis of QOF scores, can be expected to discriminate between practices (*e.g*., Records 18 (The practice has up-to-date clinical summaries in at least 80 percent of patient records); Education 6 (The practice conducts an annual review of patient complaints and suggestions to ascertain general learning points which are shared with the team); Med 9 (A medication review is recorded in the notes in the preceding 15 months for all patients being prescribed repeat medicines.). These data are available as categorical variables [54].

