### Administration of data collection

Data relating to practice organisational structure will be collected by telephone interview with the study contact at each recruited practice. This will also identify recipients of the questionnaires and will include members of the administrative staff (*e.g*., receptionist staff) and clinicians who are attached rather than employed (district nurses), although we are aware that a previous study found it was not possible to gather usable data from this latter group [3].

Questionnaires will be delivered to the practices where the research nurse (or other nominated study contact) will be responsible for their distribution, collection, and return. Reminders will be sent to practices at two-week intervals.

For clinical data held within practice computers, the research nurses will run computer queries to extract data on the total number of patients with diabetes in the practice and the number who have had the relevant clinical actions performed.

Data relating to clinician self-reported behaviour will be measured in the postal questionnaire (above) and, in addition, after a period of 12 months, a second, short questionnaire will be sent to clinical staff asking them about their behaviour in relation to the same six aspects of care over the preceding twelve months.

For the patient-reported data, questionnaires will be sent out to the 100 randomly selected patients from each practice by the nominated study contact at each participating practice. To protect patient confidentiality, a reply paid envelope, addressed to the Institute of Health and Society at Newcastle, will be provided for each patient to return their completed questionnaire directly to the research team. No reminders will be used.

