### Statistical analysis

The study will generate data on:

1. Individuals' cognitions about clinical behaviours, clinical conditions, work, team and organisational setting.

2. Organisational structure and function.

3. Clinical behaviours relating to teams of clinicians.

4. Biochemical and physiological measurements that are the consequence of the clinical behaviours, but include consequences of patient physiology and behaviour.

The analysis will explore the relationships between the predictor variables (one and two) and the dependent variables of respondents' intentions to perform behaviours, respondent's behavioural simulation, (both from survey instruments), and the clinical behaviours (three) as well as biochemical and physiological measures (four).

Where appropriate, data will be analysed as the standardised (by list size) number of patients who have had the investigation/procedure of interest performed; standardised number of patients who have their level of the investigation/procedure of interest within the accepted target range. From the patient survey we will calculate the proportion of patients in each practice who have a particular attribute (*e.g*., have been given education or training in self-monitoring).

Where appropriate (*i.e*., more than two items per measure), the reliability of the measures will be assessed prior to analysis using Cronbach's alpha to assess internal reliability and confirmatory factor analysis to identify and discard redundant items. The construct validity of the measures will be assessed prior to analysis by examining correlations between predictor variables that are expected to be similar (convergent validity) and dissimilar (discriminant validity).

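### Practice-held counts are standardised by list size rather than by the number of registered patients with diabetes, so these outcomes mix prevalence with quality of care

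*Protocol article*

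**What the plan says.** The Statistical analysis section gives two forms for practice-held data, both introduced by the words 'where appropriate'. The first: "data will be analysed as the standardised (by list size) number of patients who have had the investigation/procedure of interest performed". The second: "standardised number of patients who have their level of the investigation/procedure of interest within the accepted target range". The words 'by list size' are written for the first form and only implied for the second. No other denominator is named for these data.

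The one other use of the term is under Data relating to practice organisational structure, where it is a general characteristic of the practice: "practice demographics (including practice list size; training status of the practice, and postcodes covered".

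The number of patients with diabetes is collected. The section on data held within practice computers says "for all registered patients with diabetes we will collect data on the total number of patients with diabetes in the practice", and Administration of data collection has the research nurses extract "the total number of patients with diabetes in the practice and the number who have had the relevant clinical actions performed". The analysis text does not use this total as a denominator.

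**The concern.** The foot checks, HbA1c and BP measurements and within-target values are counted among patients with diabetes only. Dividing such a count by the whole list gives a rate that depends on how many people on the list have diabetes as well as on how well they are looked after. The stated purpose is to predict quality of care.

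Elsewhere the document uses the proportion scale. The Background describes achievement by a "target of 50% of patients having their hemoglobin A1c (HbA1c) within the target range", and the patient-survey outcomes are proportions of patients within each practice.

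Two things are at stake for the practice-held outcomes. A practice or team characteristic that goes with local prevalence could be reported as a predictor of good care when it is not. A characteristic that does predict care, but is unrelated to prevalence, would be harder to detect because prevalence adds variance to the outcome.

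**Working it through.** **1. The plan's own figure.** The Sample size section states 80% power for an effect size of 0.21 with 100 practices, 14 predictors and a 5% type one error rate. The overall F test has 14 and 100 − 14 − 1 = 85 degrees of freedom and noncentrality f2 × N = 0.21 × 100 = 21. Power is 0.802, and exactly 80% is reached at f2 = 0.209. The stated figure reproduces. It corresponds to R2 = 0.21/1.21 = 0.1736.

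**2. What the outcome measures.** Let L be list size, p diabetes prevalence and q the proportion of patients with diabetes who had the procedure or are within target.

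- Count = L × p × q
- Count / list size = p × q
- Count / registered patients with diabetes = (L × p × q)/(L × p) = q

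**3. Rank reversal (illustrative values).** The document gives only a national figure, "prevalence now over 3% [1], equating to approximately 50 patients per full time general practitioner", so the practice-level values here are assumed.

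| Practice | Prevalence | Achievement | Per 1,000 list |
|---|---|---|---|
| A | 3.0% | 85% | 0.030 × 0.85 × 1,000 = 25.5 |
| B | 4.5% | 60% | 0.045 × 0.60 × 1,000 = 27.0 |

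B has the worse care and the higher score. For these achievement levels the order reverses once B's prevalence exceeds A's by a factor of 0.85/0.60 = 1.42.

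**4. Share of outcome variance that is achievement.** With p and q independent, the squared correlation between p × q and q is

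share = CVq² / (CVq² + CVp² + CVp² × CVq²).

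The CVs are assumptions; the document gives neither. If the predictors explain R2 = 0.1736 of q and are unrelated to p, they explain 0.1736 × share of the list-size outcome. Then f2 = R2/(1 − R2), and power comes from the same F test as in step 1.

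| CV achievement | CV prevalence | Share | R2 | f2 | Power |
|---|---|---|---|---|---|
| 0.15 | 0.10 | 0.0225/0.032725 = 69% | 0.119 | 0.136 | 56% |
| 0.15 | 0.20 | 0.0225/0.0634 = 35% | 0.062 | 0.066 | 26% |
| 0.15 | 0.30 | 0.0225/0.114525 = 20% | 0.034 | 0.035 | 15% |
| 0.03 | 0.10 | 0.0009/0.010909 = 8% | 0.014 | 0.015 | 8% |
| 0.03 | 0.30 | 0.0009/0.090981 = 1% | 0.002 | 0.002 | 5% |

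The last two rows stand for near-universal measures. They are relevant because the Background reports high rates of measurement.

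**5. Sensitivity to the distributions.** A simulation used lognormal prevalence (mean 3%, CV 0.10 to 0.30) and an independent beta-distributed achievement.

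- Process measure with mean 90%, SD 5 points: share 23% down to 3%, power 17% down to 6%, and 34% to 44% of practice pairs in the wrong order.
- Target measure with mean 55%, SD 10 points: share 76% down to 26%, power 63% down to 19%, and 16% to 32% of pairs in the wrong order.

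**6. Does anything in the plan remove prevalence?** No. Weighting the regression by practice size changes how much a practice counts, not its outcome value. List size as a predictor does not adjust for prevalence. No covariate for prevalence or for the number of patients with diabetes is named.

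**The case against.** The strongest reply is that the wording is loose rather than wrong. The sentence begins with 'where appropriate', this is a condensed article, and the total with diabetes is extracted alongside each numerator, which suggests it was meant as the denominator. The study is also exploratory, and since both denominators are collected, nothing is lost if the choice is corrected before analysis. Much of this is fair. But list size is the only denominator named, the one other use of the term is for a general practice characteristic, and no criterion says when another scale would apply. If the list of patients with diabetes was meant, the text still needs the same correction.

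A reader might also infer stronger points that the document does not support:

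- *That list size in the denominator creates a spurious association with list size or staffing as predictors.* Here the count scales with the list, so L cancels. In a simulation of 200,000 practices with prevalence and achievement independent of list size, the correlation of the ratio with list size was about 0.00. The problem is confounding by prevalence, not ratio coupling.
- *That list size is also the regression weight.* The plan weights by practice size and does not define it; it could mean staff numbers.
- *That the study's outcomes as a whole fail to measure quality.* QOF scores, intention, behavioural simulation, clinician self-report and the patient-survey proportions do not use this denominator.
- *That the sample size figure is wrong.* The 0.21 is correct as calculated.

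Finally, the power loss and the confounding are separate cases. The loss in step 4 assumes predictors unrelated to prevalence; predictors related to it could instead raise the rejection rate.

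**Conclusion.** The point stands for the practice-held counts. As written, the process outcome is prevalence times achievement rather than quality of care, and by implication the within-target outcome is too. The direction of the problem follows from the definition and needs no assumption: practices can be ranked in the wrong order, and predictors related to prevalence can appear to predict care.

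The size does rest on assumptions. With a prevalence CV of 0.10 to 0.30, an achievement CV of 0.15, independence of the two, and predictors acting on achievement only, achievement accounts for 69% to 20% of outcome variance. Power for an effect of 0.21 on the proportion scale falls from 80% to between 56% and 15%. For near-universal measures (achievement CV 0.03) the share is 8% to 1%. If prevalence varies less between practices than assumed, the loss is smaller.

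**What to change.** In the Statistical analysis section, replace the list-size standardisation with the proportion of the practice's registered patients with diabetes who had the procedure or whose level is within target. State this denominator for both outcome forms. If list size was meant as the list of patients with diabetes, say so explicitly.

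The cost is one sentence. The practice computer query already returns the total number of patients with diabetes with each numerator, so no new data are needed. The sample size statement and the other outcome streams need no change on this account.

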### Dependent variables

#### Data relating to the process of care, markers of biochemical control, and QOF scores

Data for dependent variables will be collected from four sources. We will study both the performance of clinical behaviours (measuring HbA1c, BP) and the associated biochemical/physiological measurement (level of HbA1c; level of BP) accepting that there will be variability in the latter measures reflecting patient physiology and behaviour. However, these are the sort of criteria by which quality of care is judged. We will also measure clinician self-report and patient report of clinician behaviour. All dependent variables will relate to the same twelve-month period (12 months from the completion of the initial theory-based questionnaire).

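### The control outcome is a count of patients in target with no base limited to those measured, so it partly reflects measuring, and a factor related only to measuring can appear to predict control

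*Protocol article*

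**What the plan says.** All references are to the protocol article.

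- **Two things to study.** The section on process of care, biochemical markers and QOF scores says: "We will study both the performance of clinical behaviours (measuring HbA1c, BP) and the associated biochemical/physiological measurement (level of HbA1c; level of BP". The list of data types in Statistical analysis also separates clinical behaviours (item 3) from biochemical and physiological measurements (item 4). Objective 4 relates the predictors to process and to control.
- **How they become practice outcomes.** One sentence in Statistical analysis gives both: the "standardised (by list size) number of patients who have had the investigation/procedure of interest performed", and then the "standardised number of patients who have their level of the investigation/procedure of interest within the accepted target range". List size is named only in the first part. The sentence is qualified as applying where suitable.
- **Time window.** "All dependent variables will relate to the same twelve-month period (12 months from the completion of the initial theory-based questionnaire" is the rule for all dependent variables.
- **What is extracted.** The practice-computer section says that "for all registered patients with diabetes we will collect data on the total number of patients with diabetes in the practice", together with the numbers who had "a foot check; BP, HbA1c, cholesterol, and weight measured", and the levels found.
- **Source of noise acknowledged.** The plan studies levels while "accepting that there will be variability in the latter measures reflecting patient physiology and behaviour". Absent readings are not mentioned.
- **List size elsewhere.** It is among the "practice demographics (including practice list size; training status of the practice, and postcodes covered", a practice characteristic that does not depend on who was measured.

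**The concern.** A count of patients in target, over a base that does not depend on measurement, gives a patient with no reading the same score as a patient with a reading out of range. Part of the measuring outcome is then carried into the control outcome.

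Objective 4 is where this matters. A staff, team or organisational factor that only makes a practice measure more often can also be reported as a factor in better control. Two practices can also change places in the ranking because one measures more. The Background describes the quality gap as high rates of measurement but lower rates of acting on the results. A control outcome that mixes the two makes that contrast harder to see.

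**Working it through.** **Plan's own figure.** The plan gives no figure for this point. Its practice-level power statement supplies the sample size used below, and it reproduces: 100 practices, 14 predictors, effect size 0.21 and 5% type one error give 80.2% power against the stated 80%.

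**Step 1, identity.** Let m be the share of a practice's diabetic patients measured in the 12 months, and c the share in range among those measured.

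- Base of all patients with diabetes: control = m × c.
- Base of whole list size: control = p × m × c, where p is diabetes prevalence on the list.
- Base of measured patients: control = c.

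**Step 2, illustration (assumed values).**

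- Same control among measured, 60%: a practice measuring 95% scores 0.95 × 0.60 = 57%; one measuring 80% scores 0.80 × 0.60 = 48%. The 9-point gap is due to measuring alone.
- Reversed ranking: 0.95 × 0.53 = 50.4% against 0.85 × 0.58 = 49.3%. The practice with better control among measured patients ranks lower.

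**Step 3, how much of the outcome is measuring.** Assume c has mean 55% and between-practice SD 8 points, independent of m. The measuring share of the variance of m × c is approximately CV²(m) / [CV²(m) + CV²(c)], with CV²(c) = (8/55)² = 0.0212.

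| Measured (SD) | CV²(m) | Share of variance |
|---|---|---|
| 95% (3) | (3/95)² = 0.0010 | 4.5% |
| 90% (5) | (5/90)² = 0.0031 | 12.7% |
| 90% (8) | (8/90)² = 0.0079 | 27.2% |

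**Step 4, false-positive rate.** A factor with correlation ρ to m and none to c has correlation of about ρ × √share with the control outcome. For 90% (SD 5) and ρ = 0.3 this is 0.3 × √0.127 = 0.107. On Fisher's scale with 100 practices, z = atanh(0.107) × √97 = 1.06, so the chance of a two-sided 5% result is about 18%. Simulation of 100 practices with a single-factor correlation test gives:

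| Measured (SD) | ρ = 0.3 | ρ = 0.5 | Measured patients as base |
|---|---|---|---|
| 95% (3) | 9% | 18% | about 5% |
| 90% (5) | 17% | 41% | about 5% |
| 90% (8) | 32% | 70% | about 5% |

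Repeat simulations agree to within about 4 points.

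**Step 5, list size as base.** Prevalence now adds variance. With an assumed between-practice CV of prevalence of 15%, the share at 90% (SD 5) falls to 0.0031 / (0.0031 + 0.0212 + 0.0225) = 6.6%. At 25% it falls to 0.0031 / (0.0031 + 0.0212 + 0.0625) = 3.6%. The 17% at ρ = 0.3 becomes about 12% and 8%. At 95% (SD 3) the 9% becomes about 7% and 6%.

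**The case against.** **The base is inferred.** List size is attached only to the measuring outcome, and the sentence is qualified as applying where suitable. If control were standardised to measured patients, the problem would vanish. A journal article may also leave denominators to a fuller document. This stands in part: a reader might infer that the plan has a rule counting unread patients as out of target, and it states no such rule. The effect follows from the definition as a standardised count, and nothing in the document limits the base to measured patients.

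**The two outcomes can still be told apart.** This stands. A reader might infer that control is merely measuring under another name. Step 3 does not support that: measuring is about 4% to 27% of the outcome's variance, and control among measured patients dominates throughout. Nor will a measuring-only factor always appear to predict control. The Background reports high measurement, which points towards the smaller figures.

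**The measured count is already a separate outcome.** It is, and comparing the two sets of results helps. But a factor significant for both could act through measuring alone or through both routes, and the two planned outcomes do not settle which.

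**Counting all patients is a legitimate quality measure.** It is. Quality targets in the Background are expressed over patients, and restricting to measured patients drops some who may be worse controlled, which can favour practices that measure selectively. This is a good reason not to replace the all-patients version.

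**Conclusion.** The point holds in a limited form. As worded, the control outcome partly reflects measuring, although the plan lists measuring and level as separate things to study. A factor related only to measuring can therefore appear to predict control more often than the nominal 5%.

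With all patients with diabetes as the base, the rate is about 9% to 18% at 95% measured (SD 3 points) and 17% to 41% at 90% (SD 5). A wider spread would raise it, and whole list size as the base would lower it. Every one of these rates rests on assumed values: measurement rates and their SDs, 55% (SD 8 points) in range among measured, correlations of 0.3 to 0.5, and independence of measuring and control. The document gives none of them. The direction follows from the definition, but the size cannot be fixed from the document.

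**What to change.** In Statistical analysis:

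1. State the base for the control outcome as all patients with diabetes in the practice.
2. Add a companion outcome for each control measure: the number in range divided by the number with that measurement in the 12 months, analysed in the same regressions.
3. Report a factor as related to control itself, as distinct from measuring, only if the association also holds for the companion outcome.

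The cost is a few sentences and one more analysis per control measure. The extraction already covers total patients with diabetes, numbers measured and levels, so no new data source is needed. The downside is that the companion leaves out unmeasured patients, who may be worse controlled. It should sit beside the all-patients version and not replace it.
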